### Progression criteria

We will decide whether or not to proceed to a fully powered RCT using the following assessment principles and progression criteria:
Green: indicates that we have either met a criterion (in which case no modifications to the relevant aspect of the study protocol may be needed) or we are within 10% of our stated progression targets (in which case we will review the reasons for this and consider appropriate modifications to study methods)Amber: indicates that we are within 20% of our stated progression target, in which case we will critically review reasons for this and assess whether major changes to study methods are likely to realise significant improvementsRed: indicates that we are more than 20% from our target, in which case we will not, in the absence of clear extenuating circumstances, consider progression to a full trial

All the percentage changes will be measured as relative.

### Intervention feasibility

Sign up of four sites, including ≥ 50% eligible staff to complete training in delivering the intervention at each intervention siteIdentification of ≥ 50% of people who have presented to ED or ambulance service with opioid overdose or an opioid use related problemTHN kits offered to ≥ 50% eligible patients at intervention sitesSerious adverse event rate of no more than 10% difference between intervention and control sites during the live trial period and prior to the conclusion of data collection

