**Methods:**

We will carry out a feasibility study for a RCT of THN distributed in emergency settings at four sites, clustered by Emergency Department (ED) and catchment area within its associated ambulance service. THN is a peer-administered intervention. At two intervention sites, emergency ambulance paramedics and ED clinical staff will distribute THN to adult patients who are at risk of opioid overdose. At two control sites, practice will carry on as usual. We will develop a method of identifying a population to include in an evaluation, comprising people at risk of fatal opioid overdose, who may potentially receive naloxone included in a THN kit.

We will gather anonymised outcomes up to 1 year following a 12-month ‘live’ trial period for patients at risk of death from opioid poisoning. We expect approximately 100 patients at risk of opioid overdose to be in contact with each service during the 1-year recruitment period. Our outcomes will include deaths, emergency admissions, intensive care admissions, and ED attendances. We will collect numbers of eligible patients attended by participating in emergency ambulance paramedics and attending ED, THN kits issued, and NHS resource usage. We will determine whether to progress to a fully powered trial based on pre-specified progression criteria: sign-up of sites (*n* = 4), staff trained (≥ 50%), eligible participants identified (≥ 50%), THN provided to eligible participants (≥ 50%), people at risk of death from opioid overdose identified for inclusion in follow-up (≥ 75% of overdose deaths), outcomes retrieved for high-risk individuals (≥ 75%), and adverse event rate (< 10% difference between study arms).

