Numerous THN distribution programmes aiming to reduce death from opioid overdose have been implemented by drug service providers in the UK and internationally since the 1990s [15, 16]. However, a significant proportion of people at risk of opioid overdose do not engage with these services [17]. Additionally, high-quality empirical evidence to demonstrate the safety and effectiveness of THN is sparse. Observational data suggests that non-serious adverse reactions to naloxone administration are common while serious adverse reactions are rare [18]. However, the risks of inadequate response or return to a state of overdose following the administration of naloxone by laypeople remain poorly quantified [19, 20]. Moreover, the uptake of THN kits in at-risk populations remains low [21, 22] and appropriate THN intervention by peers and witnesses may not be optimal [23].

Members of the research team (CM, HS) have previously conducted a randomised feasibility study of THN distributed through the emergency ambulance service in a single-urban geographic area [24]. Their experiences, consistent with those of other researchers [25], have demonstrated that using traditional methods (e.g., telephone or postal methods) for capturing follow-up outcomes of participants in receipt of a THN kit (and of those not in receipt of a THN kit despite eligibility) is not feasible.

This paper describes a protocol for a feasibility study of THN distributed in the Emergency Department (ED) and catchment area within its associated emergency ambulance service. In carrying out the proposed study, we seek to determine the feasibility of carrying out a fully powered cluster randomised controlled trial (RCT) of THN in emergency settings using routinely collected, anonymised, and linked data to capture outcomes. Should we find that carrying out a full trial is feasible, this subsequent trial would be adequately powered to determine the safety, clinical, and cost-effectiveness of THN distribution in emergency settings.

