### Outcomes

We will measure outcomes related to the feasibility of the study in terms of the intervention and methodology, including whether we can capture sufficient data to measure clinical outcomes and health economics.

Outcomes related to the feasibility of the study include sign up of sites; proportion of eligible staff recruited and trained to deliver the intervention; proportion of eligible participants identified, number of kits issued; and the adverse event rate in intervention and control sites.

We will also assess the feasibility of collecting clinical outcomes from anonymised linked routine health records over a period of 12 months, acknowledging that feasibility will also depend on the quality and availability of routine data.

The proposed primary outcome is mortality (all deaths and those known to be opioid-related). Secondary outcomes include intensive treatment unit (ITU) admissions, ED visits, and in-patient admissions (all visits/attendances as well as those known to be opioid-related), further 999 calls as well as THN kits issued and costs. Our feasibility study will not be adequately powered to detect statistically significant differences in these proposed outcomes between intervention and control arms.

We will assess the feasibility of using routine data sources to estimate health care costs. Total NHS costs for each patient will be calculated based on the staff training costs, patient training costs, and other NHS costs (e.g. those for 999 calls, ED attendances, and admissions). Training costs will be calculated using records of completion of training, staff recall of patient training, and then combined with NHS salary data. Other NHS costs will be based on routine data for the relevant ED and ambulance service trusts.

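### The safety progression criterion has no direction, names two different events and leaves the scale of its 10% limit open, so it can be breached by chance or by fewer events at intervention sites

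*Protocol article*

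**What the plan says.** The criterion appears in three places in the protocol article.

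- **Intervention feasibility** (under Progression criteria): a serious adverse event rate with "no more than 10% difference between intervention and control sites", over the live period and up to the end of data collection.
- **Abstract, Methods:** "adverse event rate (< 10% difference between study arms". The word serious is absent and the inequality is strict.
- **Outcomes:** "the adverse event rate in intervention and control sites", again without serious.

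The **Progression criteria** section sets the bands. Green covers a criterion that is met or is "within 10% of our stated progression targets". Amber is "within 20% of our stated progression target". Red is anything further away, and red means no progression unless there are clear exceptional reasons. The section closes with "All the percentage changes will be measured as relative".

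The **Safety monitoring** section treats increased service use and death as the markers of harm. None of these sections gives an expected SAE rate or a derivation of the 10%.

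**The concern.** A progression criterion should give the same rating whoever applies it. This one leaves three things open.

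1. **Direction.** A difference counts either way. If intervention sites have fewer serious events, the literal rule is breached, which conflicts with the one-directional view of harm under Safety monitoring.
2. **Event.** Serious adverse events and all adverse events are different endpoints. The Background itself separates them for reactions to the drug: "non-serious adverse reactions to naloxone administration are common while serious adverse reactions are rare".
3. **Scale.** The sentence on relative measurement may govern only the distance from a target, or also the 10% itself. The two readings behave very differently.

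Two analysts could therefore rate the same data green or red, and could settle the reading after seeing the data. This item feeds the study's main decision and is the only progression criterion about safety.

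**Working it through.** There is no stated calculation to reproduce, because the 10% is a chosen limit without inputs. The check is how the rule behaves.

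**Inputs**
- From the article: four sites, two per arm; follow-up population at least 1520.
- Assumed: equal sites, so 1520/4 = 380 per site and 1520/2 = 760 per arm; SAE rate *p* of 2%, 10% or 30%; intracluster correlation (ICC) 0 or 0.01.

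**Bands for a 10% limit.** Green reaches 10% × 1.1 = 11%, amber 10% × 1.2 = 12%, and red is above 12%.

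**Relative reading, no true difference.** Red means an observed rate ratio above 1.12 or below 0.88. With *n* = 760, SE(log RR) = √[2(1−p)/(np)], ln 1.12 = 0.113 and ln 0.88 = −0.128.

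| p | SE | P(RR > 1.12) | P(RR < 0.88) | P(red) |
|---|---|---|---|---|
| 2% | √(1.96/15.2) = 0.359 | 0.38 | 0.36 | 74% |
| 10% | √(1.8/76) = 0.154 | 0.23 | 0.20 | 43% |
| 30% | √(1.4/228) = 0.078 | 0.07 | 0.05 | 13% |

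Exact binomial enumeration gives the same percentages. With ICC 0.01 the design effect is 1 + 379 × 0.01 = 4.79, so each SE is multiplied by √4.79 = 2.19. P(red) becomes about 88–89%, 72% and 48–49%.

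**Relative reading, true 30% reduction (ICC 0).** Only the part that is red because the intervention arm is lower is counted, with ln 0.7 = −0.357.
- p = 2%: SE = √(0.986/10.64 + 0.98/15.2) = 0.396; (0.357 − 0.128)/0.396 = 0.58, giving 72%. A further 12% is red because the intervention arm is higher by chance, and is not counted as failing on benefit.
- p = 10%: SE = √(0.93/53.2 + 0.9/76) = 0.171; 0.229/0.171 = 1.34, giving 91%.

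**Absolute reading (more than 10 percentage points), true doubling, ICC 0.** SE = √[(p₁(1−p₁) + p₀(1−p₀))/760].
- 5% to 10%: SE = 0.0134; (0.10 − 0.05)/0.0134 = 3.7, flagged about 0% of the time (at most 5% with ICC 0.01).
- 10% to 20%: the true difference sits on the limit, flagged about half the time.
- 20% to 40%: SE = 0.023; (0.20 − 0.10)/0.023 = 4.4, flagged nearly always.

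Flagged here means past 10 points. If the bands apply, red would start only at 12.

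**Would direction alone cure it?** Count only RR > 1.10 at p = 2%, no true difference: ln 1.10/0.359 = 0.095/0.359 = 0.27, giving 39% by chance. Excluding RR 1.10 with 80% power (one-sided 2.5%) at that rate would need (1.96 + 0.84)² × 2 × 0.98/0.02 ÷ 0.0953², about 84,700 per arm. A relative limit of 10% is out of reach at this size even when it counts harm only.

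**The case against.** **The relative reading is not settled.** The sentence about relative measurement follows the band definitions and may describe only distance from target; the criterion speaks of a difference, not a change. That is fair, and the chance-failure figures hold only on the relative reading. It is also part of the problem, since the text does not decide the matter.

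**No SAE rate is given.** A reader might infer from the Background that SAEs are rare and that the absolute reading never detects harm. The article does not support this. The remark on rarity concerns reactions to naloxone, not SAE rates in the follow-up population, and at control rates of 10–20% the absolute rule flags a doubling between about half the time and nearly always. The 760 per arm is likewise an assumption, because the criterion names no denominator.

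**A breach is not an automatic stop.** A reader might infer that the rule would halt a safe or beneficial intervention. Red has an override, fewer SAEs would be an obvious reason to use it, the DMC sees comparative data independently, and the article says the study is not powered for clinical outcomes. All of this stands and lowers the severity. It does not repair the rule: a criterion that needs overriding for chance or benefit gives little guidance.

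**Detail belongs in the analysis plan.** True for denominator, person-time and data source, which are not held against the article. Direction, event term and scale are different, because the article states the rule as pre-specified and states it inconsistently.

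**Conclusion.** Wrong as written; should be fixed. The missing direction and the mismatch between adverse and serious adverse events can be seen in the text without any assumption. The scale is ambiguous.

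The size is conditional on the assumed SAE rate, 760 per arm and the reading chosen. On the relative reading the rating is mostly chance at low rates and usually red under a real 30% reduction. On the absolute reading the rule has little chance of showing harm when the control rate is about 5% or less, but works reasonably at 20%. The documents do not support saying that the rule must fail on every reading, that it can never detect harm, or that it would by itself end the programme.

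**What to change.** 1. Use one event term, serious adverse events, in the abstract, Outcomes and Intervention feasibility.
2. Define the difference as intervention minus control and count only an excess at intervention sites, in line with Safety monitoring.
3. State that the limit is an absolute difference, and justify its size against the expected SAE rate. Making a relative rule harm-only is not enough.
4. Exempt this item from the relative 10% and 20% bands.
5. Report site-level rates and the between-arm difference with an interval that allows for clustering. Weigh these with the DMC's advice instead of applying a cut-off to a point estimate. The progression decision stays where the article places it.

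Items 1, 2 and 4 are wording changes. Item 3 needs an expected SAE rate, which the article does not supply. The downside is small: the rating becomes less mechanical.

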### Trial method feasibility

Identification and inclusion for outcome follow-up of ≥ 75% of people who died of opioid poisoning in the following yearMatching and data linkage in ≥ 90% of cases not dissented at the conclusion of quantitative data collectionRetrieval of primary and secondary outcomes for ≥ 75% of included participants from NHS Digital and National Welsh Informatics Service within 1 year of the projected timeline

### Safety monitoring

We will regard data on service usage (emergency and ITU admissions, and emergency attendances) and death as surrogate markers of adverse behavioural change in relation to opioid misuse, such as taking larger doses at one time. In doing so, we assume that increased rates of service usage and death correlate with an increased volume of higher risk drug-taking behaviour. We will also monitor for instances of serious adverse events, including deaths following THN use by interrogating routine health service data and also requests for data made to services on behalf of coroners across intervention and control sites. We include control sites because we expect THN to be available from specialist drug services in control sites.

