## Background

Accidental overdose related to the misuse of opioid drugs is an increasingly prevalent public health problem, and opioid-related deaths are at record levels in both the UK and North America [1, 2].

People who misuse either illicit or prescription opioids are at an increased risk of non-fatal overdose, subsequent hospital or emergency service utilisation, and death [3–5]. Non-fatal opioid overdose is associated with long-term morbidity and increased demand on health services [6, 7]. Emergency service contact for drug-related morbidity has been found to be a predictor of future episodes of poisoning or overdose [8, 9].

Naloxone is an opioid antagonist used to treat opioid overdose. Naloxone can be supplied to people at risk of opioid overdose by paramedics [10] or by laypeople in the form of take-home naloxone (THN). Typically, a THN kit comprises one or more doses of naloxone, an intramuscular needle and syringe for administering the dose, and written or pictorial instructions to explain how to prepare and administer the dose, perform basic life support, and the importance of calling the emergency services. These materials may also describe the duration of effect and hence why it is important that paramedics attend the patient as soon as possible, the safety of naloxone in terms of adverse events and overdose, and the legality of bystander administration of naloxone.

Non-experimental studies suggest that THN programmes which involve the training of laypersons to administer a naloxone dose in cases of overdose emergency are safe and effective [11, 12]. THN kits can be used by people without formal medical training in the event of an opioid overdose. Increased access to THN kits via specialist drug services in the UK and internationally has been motivated by recommendations from influential bodies, including the World Health Organization (WHO) and the British Advisory Council on the Misuse of Drugs (ACMD) [13, 14].

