#### Intervention

The TIME intervention, described here according to guidance for intervention description and replication (TIDieR) checklist [28], is Prenoxad—a multi-dose THN kit containing 2mg naloxone hydrochloride 1mg/1ml solution for intramuscular injection. This kit contains simple textual and pictorial instructions which reiterate face-to-face training each participant receives as part of the intervention. Participants will not be able to receive part of the intervention only—e.g. the training but not the kit—and so will need to consent to the whole intervention or decline the whole intervention.

The kit is manufactured by the Martindale Pharma (Woodburn Green, UK) and supported by ‘train-the-trainer’ materials for participating paramedics and ED staff developed by [name], an independent consultant. Each Prenoxad kit retails at £21.00 before VAT (value-added tax). The decision to use the Prenoxad kit, as opposed to an intranasal alternative, is supported by evidence regarding the bioavailability of naloxone following intramuscular versus intranasal administration [29, 30] and the time taken for improvement in respiratory rate to be observable [31]. We also based our decision on feedback from drug service workers who were approached in the initial setting up of the study.

Paramedics, nurses, and doctors at intervention site EDs and ambulance services registered with their respective professional bodies will be invited to participate in the study, and volunteers will be trained in delivering the intervention in accordance with the study protocol. Patient Group Directions (PGDs) will be established at participating services within intervention sites to allow non-prescribing paramedics and nurses to distribute THN kits. Training, provided in a flexible manner to suit the working practices of individual departments and services, will involve face-to-face group-based training, complemented by a ‘cascade’ approach whereby research support paramedics and nurses continue to train their peers on an ad hoc basis. Online resources produced by Martindale Pharma will be available as refresher content for staff (http://www.prenoxadinjection.com/). Training per person will take up to 15 min. Staff will complete and sign a ‘Record of Completion of Training’ form once they have been deemed competent by their trainer.

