At intervention sites, participating healthcare professionals based in the specific ED or ambulance service region and caring for patients eligible to receive the intervention will offer these patients the THN kit, with an explanation of its purpose. Patients will receive treatment as usual (TAU) and then be offered the intervention.

TAU for suspected opioid overdose involves a clinical assessment during which the healthcare staff who first come into contact with the patient seek to confirm the substance or substances which led to the overdose. Opioid overdose is assumed if the substance which led to overdose is not known and the patient presents with an altered mental state—including reduced consciousness—bradypnoea and miosis. Treatment includes prolonged and gradual administration of naloxone followed by a period of observation. Ideally, for patients attended by ambulance services, the treatment will begin at the site of the overdose and then continues at the ED following conveyance. However, patients may refuse to be conveyed should they respond to the naloxone at the scene.

In the intervention arm, if the patient consents to receiving the kit, the healthcare professional will provide training regarding the preparation and administration of the naloxone dose using the kit materials. The healthcare professional and the patient will then complete a training checklist document, to be made available to research support staff and stored as evidence that training was provided as part of the intervention.

At control sites, patients who attend for opioid poisoning or overdose or other drug-related problems will receive TAU (as described above) from ambulance and ED staff and will not be offered a THN kit.

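### Service use is read in one direction as a sign of riskier drug use, although take-home naloxone can itself change how often an overdose leads to a recorded contact

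*Protocol article*

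**What the plan says.** The Safety monitoring section of the protocol article sets the marker: "We will regard data on service usage (emergency and ITU admissions, and emergency attendances) and death as surrogate markers of adverse behavioural change". It then gives the direction in which the marker is to be read: "we assume that increased rates of service usage and death correlate with an increased volume of higher risk drug-taking behaviour". No other reading is offered.

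Four other places bear on this:

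- **Background.** The instructions in a typical THN kit explain how to "perform basic life support, and the importance of calling the emergency services". Such materials may also say "why it is important that paramedics attend the patient as soon as possible".
- **Intervention, study kit.** The protocol says of the study kit: "This kit contains simple textual and pictorial instructions which reiterate face-to-face training each participant receives as part of the intervention".
- **Intervention, control sites.** Patients there receive usual treatment and "will not be offered a THN kit". The same section notes that a patient who responds to naloxone at the scene may decline to be taken to hospital.
- **Outcomes.** The same events are proposed as outcomes: "Secondary outcomes include intensive treatment unit (ITU) admissions, ED visits, and in-patient admissions". Further 999 calls are listed beside them.

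**The concern.** A marker of drug-taking behaviour is useful only if the intervention does not itself alter how often that behaviour comes to be recorded. Here it may. A kit that urges the user to call for help can raise the share of overdoses that end in an attendance or admission, with the number of overdoses unchanged. A person whose life is saved can also attend again, which adds contacts without riskier use. In the other direction, someone revived by a bystander may decline conveyance, so an overdose that would have reached the emergency department (ED) does not.

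At stake is the safety reading of a feasibility study meant to inform a full trial. The pattern that a working intervention might well produce, more contacts and fewer deaths, has no stated interpretation. Under the stated assumption its service-use half would count as adverse behaviour.

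**Working it through.** The protocol gives no call rate, conveyance rate or overdose rate, so there is no figure of its own to reproduce. The shares below are assumptions that show how the marker behaves.

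**1. Attendance ratio with unchanged drug use.** Take equal numbers of overdoses in both arms. Let c0 be the share leading to an attendance without a kit, c1 the share with one, and k the share of intervention-arm overdoses that a kit can influence. Then

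R = [k·c1 + (1 − k)·c0] / c0 = 1 + k·(c1 − c0)/c0.

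With full reach (k = 1):

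- 33/30 = 55/50 = 77/70 = 1.10
- 60/50 = 1.20
- 65/50 = 1.30

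**2. The same ratio with limited reach.** The Sample size section expects 200 eligible contacts a year among about 2000 high-risk people at each intervention site. The progression criteria aim to offer kits to at least half of eligible patients. If every offer is accepted, that gives 100 to 200 kits per site. Take c0 = 50% and c1 = 65%, so (c1 − c0)/c0 = 0.30, and let the share of people holding a kit stand for the share of overdoses it influences.

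- Against 2000 people: k = 100/2000 = 0.05 to 200/2000 = 0.10. R = 1 + 0.05 × 0.30 = 1.015 to 1 + 0.10 × 0.30 = 1.03.
- Against the follow-up population of at least 1520 over four sites, or 1520/4 = 380 per site: k = 100/380 = 0.263 to 200/380 = 0.526. R = 1 + 0.263 × 0.30 = 1.079 to 1 + 0.526 × 0.30 = 1.158.

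So the artefact runs from about 1.5% to about 16%.

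**3. The opposite direction.** Let v0 and v1 be the shares of calls that end in conveyance. At full reach, R(ED) = c1·v1/(c0·v0). With c0 = 50%, c1 = 60% and v0 = 90%:

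- v1 = 90%: 0.54/0.45 = 1.20
- v1 = 75%: 0.45/0.45 = 1.00
- v1 = 60%: 0.36/0.45 = 0.80

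At 0.80, overdoses would have to rise by a factor of 1/0.80 = 1.25 before ED attendances merely equalled those at control sites. A true rise of up to 25% would not show as an increase.

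**4. Choice of denominator for deaths.** Suppose 5 deaths in each arm, with 50 recorded overdose contacts in one and 65 in the other. Deaths per recorded event are 5/50 = 10% and 5/65 = 7.7%, an apparent benefit with equal deaths. A ratio per recorded event is distorted by the same help-seeking, so it cannot serve as the correction.

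**The case against.** The best defence is that the authors say openly that they are making an assumption, and that a broad marker is a cautious choice for safety. Death sits beside service use in the marker, so a fall in deaths would be visible. Attendances, admissions and 999 calls are also outcomes in their own right. A Data Monitoring Committee sees comparative data, and no automatic rule hangs on the marker. The study is largely descriptive and is not powered for these outcomes. The rules for interpretation may also be set out in the analysis plan, which is not shown.

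Much of this stands, and it limits the damage. It does not remove the point, because the direction of reading is fixed in the protocol itself and placing death beside service use does not say what to conclude when the two disagree.

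Two links in the argument are inferences. The Background describes what a THN kit typically contains; the Intervention section does not list the call-for-help message for the study kit or its training. The remark on refused conveyance concerns usual treatment by ambulance staff, and extending it to bystander use is plausible but not stated.

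The loss of sensitivity from dropping attendances and admissions altogether is also a fair objection. The remedy should therefore keep them.

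**Conclusion.** The point holds in this form: service use can signal behavioural harm where there is none, or hide it where it exists, because the intervention can change the chance that an overdose becomes a recorded contact. The one-directional assumption should not stand unqualified. The size cannot be derived from the protocol. With an assumed rise in the attending share from 50% to 65%, it is about 1.5% to 16% for the reach that the protocol's own numbers suggest, and the sign for ED attendance is uncertain.

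A reader might infer four stronger things that the document does not support.

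- **That this would fail the 10% serious adverse event criterion.** Safety monitoring describes serious adverse events as something monitored in addition to the behavioural marker. Nothing says that attendances enter that rate.
- **That the effect exists at intervention sites only.** The protocol expects THN from specialist drug services in control areas, so the contrast is one of added exposure.
- **That a working kit would necessarily look harmful.** Refused conveyance could lower attendance instead.
- **That a 30% excess is realistic.** It needs a kit to influence every overdose in the arm.

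**What to change.** In Safety monitoring, replace the one-directional assumption and keep collecting every event now listed.

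- Report ED attendances and emergency admissions separately from opioid-related deaths and ITU admissions, and describe the former as measures that mix help-seeking with risk.
- Interpret them jointly with 999 calls and with opioid-related deaths per person in population B, not per recorded overdose event. The Sample size section lets contacts during recruitment bring people into the follow-up population, so say how far that denominator rests on contacts made beforehand.
- State that a rise in attendances without a rise in deaths or ITU admissions is not by itself evidence of riskier behaviour. ITU admissions are less exposed to help-seeking and survival effects only in degree, so they should be read with the same care.
- Where ambulance records show bystander naloxone before arrival, tabulate those attendances separately by arm.

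The cost is a change of wording and a little more tabulation from the same routine data. The downside is a less simple safety signal, which will need judgement when its parts disagree.
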